## Abstract

Background: The delivery of pelvic floor muscle training (PFMT) through mHealth apps has been shown to produce promising results in improving pelvic floor muscle strength and urinary incontinence (UI). However, there is limited evidence on mHealth apps designed for pregnant women who are at high risk of developing UI. This pilot study aims to evaluate the feasibility of conducting an effectiveness trial for a newly developed PFMT app among pregnant women in Malaysia. Methods: This is a prospective, single-centre, single-blind, randomised controlled pilot feasibility study: The Kegel Exercise Pregnancy Training app (KEPT-app) Trial. Sixty-four incontinent pregnant women who attended one primary care clinic for the antenatal follow-up will be recruited and randomly assigned to either intervention or waitlist control group. The intervention group will receive the intervention, the KEPT-app developed from the Capability, Opportunity, Motivation-Behaviour (COM-B) theory with Persuasive Technology and Technology Acceptance Model. Discussion: This study will provide a fine-tuning for our future randomised control study on the recruitment feasibility methods, acceptability, feasibility, and usability of the KEPT-app, and the methods to reduce the retention rates among pregnant women with UI. Trial registration: This study was registered on ClinicalTrials.gov on 19 February 2021 (NCT04762433) and is not yet recruiting.

## 1. Introduction

Urinary incontinence (UI) is defined as involuntary urinary leakage [1]. A recent cross-sectional study in a Malaysian primary care centre reported that 40.9% of pregnant women had UI [2], which is similar to a meta-analysis that reported 41.0% (range of 9–75%) of 88,305 pregnant women had UI based on 44 included studies [3].

UI during pregnancy has resulted in slight to moderate impairment of quality of life (QOL) [4]. UI poses a risk of a person’s physical, functional, and psychological morbidities [5]. Pregnant women with UI may experience negatively impacted QOL in terms of their social-emotional relationships, difficulty in doing exercise and sport, employment issues, restrictions when travelling, sleeping disturbances, and difficulty during prayers [6]. This will be expected especially in Malaysia, where it is a Muslim country and to be dry before ablution and during the prayers is mandatory for the five times daily prayers.

Pelvic floor muscle training (PFMT) or Kegel exercise is an essential exercise to strengthen pelvic floor muscles among pregnant women [7]. PFMT during the first pregnancy may help shorten the first and second stage of labour [8]. PFMT during pregnancy can prevent pelvic floor dysfunction, for example, urinary incontinence in late pregnancy and the early postpartum period [9]. Unfortunately, despite affecting their daily activities, only one-tenth (13.1% of 407 pregnant women) seek help due to the misperception that UI would resolve itself [4].

The barriers in performing PFMT among pregnant women can be divided into several factors, for example, normalisation of having UI [10], limited resources [10] that lead to limited knowledge of PFMT [2], and misconception that PFMT will lead to miscarriage [10]. Correct and reliable information on PFMT must be easily accessible via the internet or the mHealth app for the target population.

Acquiring correct PFMT skills may be challenging for pregnant women, resulting in poor adherence [11]. First, they must understand the basic facts about UI, adopt the correct attitude towards PFMT, and learn and practice PFMT from a skilful instructor. Following this, their confidence will be built up to obtain good self-efficacy of PFMT. They will then be able to implement and incorporate PFMT into her daily activities to ensure its retention and sustainability. Therefore, a suitable and well-designed intervention would help motivate pregnant women in adopting PFMT into their daily activities.

There are barriers from health personnel when discussing and providing instructions of PFMT as this is not routinely practiced [11]. These factors will reduce the availability of the services and affect the accessibility of PFMT to pregnant women [12]. However, despite being accessible, the acceptability of PFMT services is crucial to ensure that the pregnant women are willing to learn and adhere with PFMT. Therefore, an innovative way that involves easy, low-risk, and proven strategies may improve the availability, accessibilities, and acceptability of PFMT among pregnant women.

Mobile health (mHealth) is defined as “a medical and public health practice supported by mobile devices, such as mobile phones, patient monitoring devices, personal digital assistants, and other wireless devices” [13]. mHealth has many potential benefits in health behaviour interventions. Its strengths lie in its ease of access and user-friendliness, resulting in its widespread adoption worldwide [14]. Furthermore, pregnant women using the apps will have timing flexibility, save money, and feel less embarrassment [15,16,17].

mHealth apps have shown their effectiveness in self-management of pregnancy, improving healthcare delivery, improving cholesterol levels, improving mood and energy levels of pregnant women, and less hospital visits among the high-risk pregnancy groups [18]. mHealth apps may include some features such as audio guidance for PFMT, which contributes to its effectiveness in improving compliance among pregnant women [16]. Tät app has proven its pragmatic effectiveness for self-management of incontinence among non-pregnant women, which has been downloaded up to 65,000 times during its study period [19]. DiárioSaúde app was designed by utilising operant conditioning among 17 non-pregnant women with an improvement in incontinence reported with PFMT adherence [20]. Hence, PFMT intervention may be delivered via mHealth apps to improve the self-efficacy and adherence towards PFMT among pregnant women with an appropriate implementation strategy [21].

Limitations and concerns of mHealth apps need to be addressed when pregnant women download the apps, such as its content accuracy, risk of confidentiality breaches, privacy and security, and the lack of central regulation and professional involvement in their development [22]. Even though 32 out of 120 apps related to PFMT, which included 15 paid apps and 17 free apps, are available in official stores, only a limited number of PFMT apps related to pregnant women have undergone clinical trials [23]. Professionals and researchers need to develop PFMT apps to ensure pregnant women’s safety and to improve the quality of maternity care.

Successful implementation of PFMT in maternity care is influenced by three crucial factors: (1) personal factors, (2) organisational factors, and (3) contextual factors [24]. Personal factors include the motivation of the pregnant woman, her perception towards the value of the new behaviour, and PFMT skill development [24]. Organisational factors involve stakeholder engagement in adopting the intervention and service provider involvement in the design and development of the intervention [24]. Meanwhile, the contextual factors consist of adapting the intervention to fit into the current maternity service provision and the capacity to accommodate for changes [24]. Subsequently, a pilot study should be able to investigate any barriers or issues from these three factors. 

The pilot study is an essential step before implementing a full-scale phase III trial [25]. Before a full-scale study is conducted, a pilot study can help to assess the feasibility of the key processes of the main study, such as evaluating the recruitment rates. Pilot studies also help in identifying possible problems that may crop up during the main study. These may include time and resource issues or human and data management issues related to implementing the intervention in a busy primary care clinic. Finally, a pilot study can provide information on the preliminary effectiveness and the related processes of the intervention, such as the appropriate duration of daily exercise to have a significant PFMT adherence among pregnant women [25]. 

We will conduct a pilot and feasibility study to assess the feasibility, acceptability, and usability of a PFMT mHealth app. The app is a Kegel Exercise Pregnancy Training app (KEPT-app), which is compatible with Android version, developed by Pheon Tech, Selangor, Malaysia. At the time of writing, KEPT-app is undergoing usability evaluation via heuristic assessment to assess the user interface, cognitive walkthrough to assess the learnability of the app, and think-aloud to assess the user’s experience in using the app. The usability of this app in the clinical setting will be evaluated during this pilot feasibility study.

Initially, we published the study protocol for the KEPT-app trial [26]. The trial would have utilised a cluster RCT design, which would have involved ten primary care clinics. However, due to unforeseen circumstances related to the COVID-19 pandemic, including social restrictions to conduct research at public healthcare facilities, changes were required to conduct the research. Therefore, a smaller scale feasibility trial was planned, focusing on one health clinic instead of the original multicentre trial. This trial was needed to identify possible barriers and modifications required to enable the full study to be conducted as a pragmatic RCT.

This pilot study aims: (1) to examine the acceptability and feasibility of the KEPT-app, to determine the appropriate training time in achieving the advanced skills level; (2) to determine the dropouts from the control group and to assess any dissatisfaction among the control group; (3) to assess recruitment rate, to determine the reasons from dropout participants (if any); and (4) to assess the preliminary effectiveness in knowledge, attitude, practice, and adherence to PFMT, PFMT self-efficacy, PFMT adherence, UI, and quality of life. The cost-effectiveness analysis will be performed to assess the health economy of the KEPT-app from the societal perspectives for treating UI among pregnant women. To our best knowledge, KEPT-app is the first designed app for all types of parity among incontinent pregnant women. Therefore, a pilot feasibility study is crucial to assist in the feasibility of the future KEPT-app trial study

## 2. Materials and Methods

Design overview: This pilot study will use a single-blind, single-centre, parallel, randomised controlled trial (RCT) design that will incorporate individualized treatment flexibility, as in a real-world setting, and provide the future study’s feasibility process [26]. The study protocol was designed and reported according to CONSORT (Consolidated Standards of Reporting Trials) extension for randomised pilot and feasibility trials [27,28].

Participants (eligibility criteria): The eligible participants are: (1) pregnant women aged over 18 years old, (2) any parity at 26–27 weeks’ gestation, (3) with either stress UI or mixed UI according to the International Consultation on Incontinence Questionnaire—UI Short Form [29,30], and (4) Malaysian citizens. Other citizens will be excluded as the primary language used in this study will be Malay, the national language of Malaysia.

Additionally, pregnant women with chronic medical problem(s) before pregnancy, complicated pregnancies, or conditions with which it is not advisable to practise PFMT will be excluded.

Recruitment and withdrawal: This study will be conducted at one primary care clinic in the Hulu Langat district under the same management as the future study [26]. The recruitment process will follow the future study, whereby pregnant women will be invited from a poster announcement [26]. They will then contact the research assistant (RA) via WhatsApp or Short Message System (SMS) for the eligibility screening process. Once a pregnant woman is eligible to join the study, the RA will provide her with a link to download the app for the consent forms. (Figure 1)

All study participants can withdraw at any time during the trial with or without any reasons. The RA will contact those who have withdrawn to obtain reasons and their experiences joining this pilot study. This finding will be analysed and given as input into the barriers that will add to future study modifications.

For the sample size, an analysis suggested that 12 participants per group is an appropriate sample in a feasibility study [31] and another review stated that 15 participants per group could be adequate for moderate effect sizes [32]. A pilot randomised controlled trial for an expected small effect size should have 25 participants per arm [33]. However, considering a possible 20% dropout rate, the final sample size will be 64 participants with 32 participants per arm.

Regarding the randomisation and blinding, a random allocation will be applied to ensure the balance between the intervention and control groups. The RA will perform the stratified randomisation with two lists of identification numbers with primigravida or multigravida, because gravida is a significant prognostic risk factor in UI [34]. After the two lists have been made, the RA will use permuted blocks of two or four via RRApp, a randomisation app [35] for random allocation into the intervention and control group. The assigned group allocations will be concealed in an opaque envelope assigned by the nonresearchers in this study. Although study participants will not be blinded, both RA and the researchers who are performing statistical analysis will be blinded to the study participants’ allocation to fulfil the single-blind study criteria [36]. 

Study participants will receive the intervention (KEPT-app) to improve their pelvic floor muscle training in addition to their usual antenatal care. KEPT-app is designed to educate pregnant women on PFMT via step-by-step training with the capability element to improve their confidence and skills (beginner, intermediate, and advance skills). Pregnant women are encouraged to continue to adopt PFMT throughout pregnancy until the postpartum period. The details of the mHealth app content were developed based on the need assessment gathered from the cross-sectional study [2]. It was conducted to identify the need for PFMT and understand the knowledge, attitude, and practices towards PFMT.

KEPT-app is derived from a comprehensive theoretical framework that is Capability, Opportunity, and Motivation-Behaviour (COM-B) model and delivered using the persuasive technology (PT) approach [37,38]. The COM-B model is an extension and assimilation of 14 domains from the Theoretical Domains Framework (TDF) [39]. An additional theory for the KEPT-app will be the Technology Acceptance Model, whereby the usefulness and the ease of use will increase the respondents’ intention to continue using the app [40].

Perceived usefulness refers to “the degree to which a person believes that using a particular system would enhance his or her job performance” and perceived ease of use indicates “the degree to which a person believes that using a particularly stem would be free of effort” [40]. Meta-analysis highlighted that perceived usefulness is the most common predictor of mHealth use and showed a medium-strength relationship with perceived ease of use [41]. Therefore, the mHealth app with a simple design will encourage the users to use it, and their perception of effortless use the app will motivate them to continue using the app. The relationship between Technology Acceptance Model (TAM), Persuasive Technology, and COM-B model is illustrated in Figure 2.

The KEPT-app, developed for the Android version 9.0 operating system, consists of the following main user interfaces: (1) the main login page, (2) the PFMT training video, (3) the exercise module with a timer, (4) a calendar for users to chart their wet days and completed exercise, and (5) a score board. At the time of writing, the KEPT-app prototype is undergoing usability evaluation by both the experts in informative technology and health informatics and from the end-users (pregnant women with UI). Feedback from the usability evaluation will be used to revise the app. The final KEPT-app will then be tested during this feasibility study. The app will be delivered only to the study participants and not through the official stores.

The control group will receive antenatal care as usual during the intervention period and access to install the app after 36 weeks of pregnancy. Routine antenatal care follow-up will be based on the Ministry of Health guidelines [42]. 

Primary outcomes are the outcomes relevant to the acceptability of the KEPT-app. Acceptability and feasibility of the KEPT-app is the satisfaction and agreeableness of the app’s pregnant women [43]. Acceptability is crucial as it affects the success of an implementation phase [44]. The acceptability will be assessed for its content, complexity, and comfort [43]. 

The KEPT-app feasibility will be defined as KEPT-app’s extent of successfully being used or carried out in a primary care clinic setting [45]. The app feasibility will be assessed along with the usability assessment, which can assess the ease of use, interface, satisfaction, and mHealth app usefulness [46]. Additionally, the PFMT education video embedded in the app should assess its understandability and actionability [47]. 

Secondary outcomes are as follows; (1) feasibility of recruiting the study participants, which include numbers and proportions of participants recruited, screened, consented, and numbers with their reasons for withdrawals; (2) face validation on the educational video embedded in the app; (3) appropriate training time in achieving the advanced skill level; (4) control group’s barriers continuing the study; (5) barriers and suggestions for using the app; (6) the knowledge, attitude, and practice of PFMT; and (7) quality of life.

Training time will be recorded automatically via the app and a reminder will be delivered (during the evening) if no PFMT is recorded on that day. There will be three training skills: beginner (2 s each contraction), intermediate (6 s each contraction), and (10 s each contraction). The pregnant women are scheduled for ten repetitions each set and must complete three sets every day. The time recorded will be analysed using the algorithm to measure which training skills will change their self-efficacy and adherence.

It is essential to determine the KEPT-app’s preliminary effectiveness to improve the PFMT skills of pregnant women. The time recorded by the pregnant women will be analysed with the self-efficacy improvements and adherence towards PFMT. Additionally, the recorded time will be analysed with the UI changes within the group.

Additional qualitative data collection will be used to further understand any barriers or suggestions from the study participants. The expenditures during the study, for example, the cost of absorbent pads, participant’s salary, and cost of laundry where applicable, will be compared between the groups to assess the cost-effectiveness.

Trial feasibility (treatment fidelity) is crucial to ensure that PFMT is performed by the participants according to the system log recorded. The monitoring must be continuously performed to ensure the treatment fidelity. Treatment fidelity describes “the methodological strategies used to monitor and enhance the reliability and validity of behavioural interventions” [48]. Therefore, the RA must actively monitor the system log activities (training time) and immediately inform the researcher if any system failure or no activities are recorded by the patients.

The adherence to the training time is when the pregnant women complete 80% of the expected training time, which will be continuously recorded after they watch the video [49]. The calendar apps method will record their PFMT, and if they have not logged the data, a reminder will be delivered automatically. The adherence rate data will inform future studies when the best time is to send the booster or reminders. Any errors or issues will be recorded, and the system update or debugging will be recorded for further analysis.

To assess the trial feasibility of the recruitment of study participants and retention rates, the total number of study participants who can be recruited, screened, and interested in participating within one month will be examined. The researchers will assess the study feasibility by reviewing the timing log data recorded during the pilot study. This recruitment process is critical as there will be no researcher on-site to promote this study due to the uncertainty of the restricted movement due to the COVID-19 pandemic. 

Any dropout or defaulter will be traced and contacted. The number of withdrawals will be recorded and descriptively analysed. There will be no further analysis for the dropouts with per-protocol (PP) analysis and intention-to-treat (ITT) analysis to evaluate the influence of missing data as this is not an effectiveness study.

We will perform primary and secondary outcome measures at three time points during the trial to assess the trial feasibility in collection of outcome data—at enrolment into the study, a baseline assessment will be recorded, and one-month and two-months post-intervention, an assessment will be recorded accordingly for both groups.

The participant feedback towards this app will be assessed via qualitative data collection after the study ends. This feedback will provide the input regarding the trial feasibility based on the barriers to the implementation of the intervention. Pregnant women will add their opinion on the barriers and difficulties and their suggestions in improving this app. 

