In evaluating the cost analysis study, the data from the two-month follow-up will be extrapolated to one year for the calculations. We will collect each participant’s training time; incontinence aids, for example absorbent pads; and laundry (if applicable) at baseline and at a two-month follow-up among all the participants [54]. We will utilise the International Consultation on Incontinence Modular Questionnaire on Lower Urinary Tract Symptoms and Quality of Life to measure their quality of life to calculate the quality-adjusted life years (QALYs) gained [54].

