### 2.2. Statistical Analysis

The primary analysis of this pilot study will be by descriptive analysis to concentrate on the feasibility outcomes. The recruitment number and the proportion of participants screened, consented, and randomised will be presented. Additionally, the information of the dropouts will be presented with their reasons in the results.

The results of study outcomes and validation of educational video will be analysed. Exploratory analysis of the effect sizes for PFMT adherence will be conducted by mixed-effects regression analyses, controlling for significant baseline characteristics, such as age, parity, educational status, and income status. For the cost-effectiveness analysis, expenditures during the study will be compared between the groups using the multiway sensitivity analysis.

As the data will be sent via the app, the system will collect the data and store it in a secured and encrypted cloud storage. The researcher (blinded) who has been trained with a statistical analysis program will analyse the data using the Statistical Package for the Social Sciences version 27.0, IBM, New York, United States of America [55,56].

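### Control access to the app opens after 36 weeks of pregnancy with no stated link to the two-month assessment, so a late assessment can fall after access has opened

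*Protocol article*

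**What the plan says.** All of this is in the protocol article.

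- **Entry** (section 2, eligibility): "any parity at 26–27 weeks’ gestation".
- **Control arm** (section 2): "antenatal care as usual during the intervention period and access to install the app after 36 weeks of pregnancy". The length of the intervention period is not given.
- **Release of the app** (section 2): "The app will be delivered only to the study participants and not through the official stores".
- **Assessments** (section 2): baseline at enrolment, then "one-month and two-months post-intervention, an assessment will be recorded accordingly for both groups". Table 1 lists incontinence, adherence, self-efficacy, knowledge/attitude/practice and quality of life at all three time points.
- **Costs**: section 2 says that expenditures "will be compared between the groups to assess the cost-effectiveness". Section 2.1 collects training time, incontinence aids and laundry "at baseline and at a two-month follow-up among all the participants" and projects the two-month data to one year.
- **Non-responders** (section 2): "Any dropout or defaulter will be traced and contacted".
- **Analysis** (section 2.2): the primary analysis is descriptive. "Exploratory analysis of the effect sizes for PFMT adherence will be conducted by mixed-effects regression analyses".

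**The concern.** Two clocks run side by side. Access for controls follows gestational age, while the last assessment follows time since enrolment. The 36-week rule looks meant to come after the last assessment, and for a punctual participant it usually does. But the order is a by-product of the dates, not a rule. The clause on usual care suggests that controls stay off the app while the intervention period runs. Because that period has no stated length, the clause does not tell staff what to do with a control who is past 36 weeks and has not yet been assessed.

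A control who answers after access has opened may already have seen the training video and begun the exercises. That would pull the two arms together at two months. For the cost items there is no one-month measurement to fall back on, and the two-month values are carried forward to a year.

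**Working it through.** The article gives no figure for gestational age at the last assessment, so there is none to reproduce. The check places both clocks on one scale, in days of gestation.

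**Inputs**
- Entry: 26+0 = 182 to 27+6 = 195 (completed weeks, 14 possible days), or to 27+0 = 189 (narrow reading, 8 possible days).
- Access: from 36+0 = 252, or from 37+0 = 259 if 36 completed weeks must have passed in full.
- Two months: 8 weeks = 56 days, or calendar months of 59 to 62 days. The central value is 61 (365.25/12 × 2 = 60.9).
- Start of the two months: enrolment (assumption).
- Delay: 0, 7 or 14 days. The article gives no visit window, so 7 and 14 are assumptions.

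**Formulas**
- Assessment day = entry + follow-up + delay.
- Overlap if the assessment day is later than the access day.
- Margin for the latest entrant = access day − assessment day.

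**On time, 61 days.** The assessment falls at 182 + 61 = 243 (34+5) for the earliest entrant. For the latest it falls at 195 + 61 = 256 (36+4), or at 189 + 61 = 250 (35+5) on the narrow entry reading.

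| Entry to / access from | Margin, 61 days | Margin, 56 days |
|---|---|---|
| 27+6 / 36+0 | 252 − 256 = −4 | 252 − 251 = +1 |
| 27+0 / 36+0 | 252 − 250 = +2 | 252 − 245 = +7 |
| 27+6 / 37+0 | 259 − 256 = +3 | 259 − 251 = +8 |
| 27+0 / 37+0 | 259 − 250 = +9 | 259 − 245 = +14 |

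Only the first reading gives an on-time overlap, and only with calendar months. It runs from 195 + 59 − 252 = 2 days to 195 + 62 − 252 = 5 days for the latest entrant, and touches 2 to 5 of the 14 entry days.

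**Late, 61 days.** Entry days with overlap, and the most days of possible access before the assessment:

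| Entry to / access from | 7 days late | 14 days late |
|---|---|---|
| 27+6 / 36+0 | 11 of 14 (max 195 + 68 − 252 = 11) | 14 of 14 (max 195 + 75 − 252 = 18) |
| 27+0 / 36+0 | 5 of 8 (max 189 + 68 − 252 = 5) | 8 of 8 (max 189 + 75 − 252 = 12) |
| 27+6 / 37+0 | 4 of 14 (max 195 + 68 − 259 = 4) | 11 of 14 (max 195 + 75 − 259 = 11) |
| 27+0 / 37+0 | 0 of 8 | 5 of 8 (max 189 + 75 − 259 = 5) |

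With 8-week months, entry to 27+6 and access from 36+0, the counts are 6 of 14 (7 days late) and 13 of 14 (14 days late).

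**One-month assessment.** Even the latest entrant reaches it at 195 + 31 = 226 (32+2), 26 days before 36+0, so it is not at risk.

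These are counts of entry days, not of women. The article does not say how entries spread over the two weeks or how many controls will answer late.

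**The case against.** The case against is substantial, and much of it stands.

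- **The schedule works as written for punctual participants.** Entry at 26–27 weeks plus two months ends at about 34 to 36 weeks. On-time overlap needs three readings at once and disappears if any one changes. This stands. A reader might infer that controls will routinely have the app at their last assessment; the documents do not support that.
- **Gestational age is not the only condition in the sentence.** The usual-care clause is an implied guard. This stands, so it would be too strong to say that nothing but gestational age governs access. The guard is of unstated length, however, and does not settle the case of an unassessed control past 36 weeks.
- **The delays are assumed.** No passage says that overdue assessments will be accepted weeks late. Tracing defaulters shows that non-response is expected, not that late answers will be used. Visit windows may well be set in the full protocol. This stands as a limit on size.
- **Access is not use.** A control would have to install the app, train and change within days. This stands: the tables count days of possible access and do not estimate bias.
- **The wording about assessments could be read to widen the gap.** Taken literally, "one-month and two-months post-intervention, an assessment will be recorded accordingly for both groups" could mean two months after the intervention has ended, with a longer overlap. Section 2.1 speaks simply of a two-month follow-up, and no length of intervention is given from which to count, so that reading is not adopted.
- **The consent link.** Every eligible woman gets a download link for consent before allocation. A reader might infer that controls hold the training content from the start. The article does not say whether that content is locked for controls, so no conclusion is drawn from it.

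**Conclusion.** The point holds in a limited form. The stated access rule is not linked to the two-month assessment, and the margin between the two is thin. On-time overlap is nil under most readings and at most 2 to 5 days for the latest entrants under the least favourable one. A delay of one to two weeks, which is assumed, could put the assessment after access for many controls.

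Any dilution is likely small. It would touch only the exploratory two-month between-group comparisons and the cost data. The primary acceptability and usability results and the one-month comparisons are unaffected. The conclusion rests on counting two months from enrolment. It is an inexpensive improvement to the rule, not an error that undermines the pilot.

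**What to change.** In section 2, in the sentence on the control group, state that controls get access after 36 weeks of pregnancy or once their two-month assessment is completed, whichever is later. Add a fixed cut-off, for example 14 days after the assessment is due, after which access opens anyway and any later response is left out of the two-month comparison. Apply the same cut-off to responses in both arms, so that the rule does not itself create a difference.

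The article defines no window, so the cut-off has to be chosen. No visit moves and the sample size does not change. Because the app is given only to participants, the study can hold back its release.

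The costs are a slightly longer wait for a control who answers late and the loss of the few responses after the cut-off. With 61 days and entry at 27+6, access opens no later than 195 + 61 + 14 = 270 (38+4). A 7-day cut-off would give 195 + 61 + 7 = 263 (37+4). The shorter cut-off leaves a waitlisted woman more of her pregnancy to use the app, at the price of more excluded late answers.
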